**Statistical analysis:**

The SPSS Package version 25 for Windows (SPSS, Inc., Armonk, NY: IBM Corp) will be considered for the analysis.

Data will be tested for homogeneity and a 3 x 2 MANOVA mixed design was used for comparing variables in different groups and measurement times.

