**Subjects**

This study will be conducted in accordance with the Declaration of Helsinki after approval is obtained from the research ethics committee, Faculty of Physical Therapy, Cairo University, Egypt. The protocol will be registered in the ClinicalTrials.gov.

Sample size was calculated through estimates for the means and standard deviations that will be obtained from a pilot study on 15 patients to receive the treatment protocol.

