**Outcome measures:**

**Primary outcome:**

The temporomandibular opening index (TOI) is calculated by the formula ^23^ :

TOI= Passive opening _mm_ -Maximum voluntary opening _mm_ X 100

Passive opening _mm_ + Maximum voluntary opening _mm_

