**Secondary outcomes:**

1. Surface EMG (sEMG):

For recording, a surface electromyograph (Myotronics-Noromed, Inc., Tukwila WA, USA), with 8-channels, simultaneous acquisition, common grounding to all channels, and filters of 50 Hz electromyography with disposable electrodes was used.

Subjects will be seated on chairs with back and head rests to allow assessment from a relaxed position.

The right masseter (RM), left masseter (LM), right anterior temporal (RAT), left anterior temporal (LAT), right sternocleidomastoid (RSM), and left sternocleidomastoid (LSM) muscles will be recorded.

Electrode positions are adopted from Castroflorio et al., 2005 for the left and right masseter muscles (LM, RM) and the left and right anterior temporal muscles (LAT, RAT) ^20^ as well as Falla et al., 2002 for the left and right sternocleidomastoid muscle (LSM, RSM). ^24^

The ground electrode will be positioned on the forehead as a common reference to the amplifier’s differential input.

1. Visual analogue scale

Pain intensity will be assessed by the Visual Analogue Scale (VAS) where no pain is rated as 0 mm and worst possible pain as 100 mm.^25,26^

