**Procedures**:

Laser group: A low-level gallium arsenide diode (Biolase, USA) at a 940 nm wavelength with 0.2 W output power and 2 J energy will be used. The device will be calibrated, and the probe to be disinfected prior to every treatment.

The Masseter and Temporalis muscles will be bilaterally assessed with constant pressure to define tenderness.

LLLT will be applied perpendicular to each tender point of the intended muscles for 10 seconds with an energy density of 2.5 J/cm^2^.

Sessions will be scheduled 3 days a week (every other day) over a period of 4 months.

1. Occlusive splint:

A soft occlusal splint (vacuum-formed) made from a 2-mm-thick elastic rubber sheets was used. ^27^

Splints will be individually designed for the upper arch of each patient. An alginate imprint of the maxillary arch was taken to fabricate a master cast of the maxilla.

Participants will be instructed to wear the splint at all times except during mealtimes and oral hygiene.

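### The only analysis named, a mixed-design MANOVA, is complete-case unless values are imputed and gives the primary outcome TOI no model of its own

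*Protocol*

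**What the plan says.** The Statistical analysis section has two sentences. The first names the package: "The SPSS Package version 25 for Windows (SPSS, Inc., Armonk, NY: IBM Corp) will be considered for the analysis". The second mentions a check of homogeneity and then the one inferential method: "a 3 x 2 MANOVA mixed design was used for comparing variables in different groups and measurement times". It does not say which factor has three levels, which outcomes enter the model together, or which SPSS procedure fits it.

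The outcomes are listed under Outcome measures. The primary outcome is one variable: "The temporomandibular opening index (TOI) is calculated by the formula". The secondary outcomes are surface EMG of six muscles, a list that ends "left anterior temporal (LAT), right sternocleidomastoid (RSM), and left sternocleidomastoid (LSM) muscles will be recorded", and pain: "Pain intensity will be assessed by the Visual Analogue Scale (VAS". No outcome is given an analysis separate from the MANOVA.

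Under Subjects, the sample size rests on pilot estimates: "Sample size was calculated through estimates for the means and standard deviations that will be obtained from a pilot study on 15 patients". No sample size, power or dropout allowance is given.

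**The concern.** A MANOVA over repeated measurements holds each patient's values as one response vector. If one entry of the vector is missing and nothing is imputed, the whole patient leaves the model. This has two consequences of different strength.

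- **Missed assessments.** Even with TOI as the only outcome in the model, a patient who misses one assessment loses the TOI values that were measured. This does not depend on how the outcomes are grouped.
- **Missing secondary values.** If TOI, VAS and sEMG share one model, a failed electrode or a blank VAS removes a patient whose TOI is complete. A secondary measurement then decides who counts for the primary outcome.

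At stake are the power of the TOI comparison and, if the losses are related to outcome or arm, its standing as a comparison of the groups as randomised.

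**Working it through.** The protocol states no sample size, power or missing rate, so there is no figure to reproduce. What follows shows the mechanism and a range under stated assumptions.

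**Inputs from the protocol.** One TOI variable, one VAS variable and six recorded muscles. If each muscle gives one summary value, that is 1 + 1 + 6 = 8 variables. The 3 x 2 layout allows two or three measurement times, so both are shown.

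**Assumed.** A missing rate p per value; the protocol gives none.

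**Mechanism.** In a simulated MANOVA with 40 patients and 16 responses (8 variables x 2 times), one value was removed from each of two patients. The fit used 38 rows. This was run in Python's statsmodels, not in SPSS.

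**Share of patients kept.**

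- Joint model, values missing independently: (1 − p)^(8 x times)
- TOI alone, complete cases: (1 − p)^times
- Joint model, values missing only by whole visit: (1 − p)^times, the same as TOI alone

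| p (assumed) | Joint, independent, 2 times | Joint, independent, 3 times | TOI alone or whole-visit, 2 times | TOI alone or whole-visit, 3 times |
|---|---|---|---|---|
| 0.5% | 92% | 89% | 99% | 98.5% |
| 1% | 85% | 79% | 98% | 97% |
| 2% | 72% | 62% | 96% | 94% |
| 5% | 44% | 29% | 90% | 86% |

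For example, at 2%: 0.98^16 = 0.724, 0.98^24 = 0.616, 0.98^2 = 0.960 and 0.98^3 = 0.941.

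**Power, for illustration only.** Assume a standardised difference of 0.8, two-sided 5% and 80% power. Then n = 2 x (1.96 + 0.842)^2 / 0.8^2 = 24.5, or 25 per arm. With a fraction f of patients kept, power is about Φ(0.8 x √(25f/2) − 1.96):

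- f = 0.85 gives Φ(0.65) = 74%
- f = 0.79 gives Φ(0.55) = 71%
- f = 0.61 gives Φ(0.25) = 60%
- f = 0.98 gives Φ(0.84) = 80%

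The first two fractions are the joint model at 1% missing with two and three times. The third is close to the joint model at 2% with three times. The last is TOI alone at 1% with two times.

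**The case against.** The strongest reply is that this is a missing-data point under another name. The protocol never says that incomplete patients are deleted, and imputation and analysis sets are commonly left to an SAP, which is not shown here. That silence is indeed no finding. What stands is narrower: the protocol does fix a method, that method is complete-case by default, and it is the only one offered for the primary outcome. An SAP that follows the sentence inherits the problem unless it adds imputation.

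Stronger readings that a reader might infer are not supported:

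- **That naming SPSS implies deletion.** It does not. SPSS 25 also fits mixed models. The point rests on the MANOVA sentence.
- **That one lost sEMG channel certainly removes a patient from the TOI comparison.** This needs TOI and sEMG in the same model. A MANOVA on variables in the plural suggests that, but the protocol does not state it. Nor does it define an sEMG summary variable, so eight variables is a count made here.
- **That the laser schedule makes losses differ between arms.** The schedule reads "Sessions will be scheduled 3 days a week (every other day) over a period of 4 months", about 3 x 52/12 x 4 = 52 sessions, and no visit schedule is given for the splint arm. But these are treatments, and a missed treatment is not a missed outcome assessment. Unequal loss is possible; its size and direction cannot be had from the protocol.
- **That the comparison is therefore biased towards patients who improve.** Values missing independently at random cost power without biasing the comparison. Bias needs loss related to outcome or arm, which nothing in the protocol documents.
- **That the joint model must lose far more patients than TOI alone.** The large gaps come from assuming independence. The EMG channels are acquired simultaneously and a missed visit takes all outcomes with it, so much of the missingness would cluster. If all of it did, the excess loss would be zero.

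**Conclusion.** The concern holds in a limited form. The one method named uses only complete patients unless values are imputed, and TOI has no separate model. The loss from missed assessments follows on any grouping of outcomes. The loss from missing VAS or sEMG values is conditional on a joint analysis, which is a likely reading of the wording but not a stated one.

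The size is unknown. At an assumed 2% missing per value, the excess loss of the joint model over TOI alone runs from zero (whole-visit missingness) to 96% − 72% = 24 percentage points with two times, or 94% − 62% = 32 points with three (full independence). The truth probably lies between these. The power figures rest in addition on an assumed effect and sample size. The change is worth making because it is cheap and protects the only primary comparison.

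**What to change.** Replace the MANOVA for the primary comparison with a linear mixed model for TOI alone. It should have terms for arm, visit, arm by visit and baseline TOI, and be fitted in all randomised patients in their assigned arm with every available TOI value. Use separate models of the same form for VAS and for each sEMG variable. Add one sensitivity analysis for missing TOI, because the mixed model is valid only if missingness can be explained by the data observed.

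If there is only one follow-up assessment, this model reduces to analysis of covariance, and a patient without follow-up TOI adds nothing to it. The gain is then the separation of TOI from the other outcomes, and the sensitivity analysis has to cover the rest. With two follow-up assessments, a patient who misses one still contributes the other.

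The MIXED procedure in SPSS 25 can fit these models, so the software stays the same. The cost is a change of statistical wording and slightly more analysis work. Continued measurement of patients who stop treatment would be a change of trial conduct and is not needed for this change.

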**Purpose of the study**

To assess the efficacy of low-level laser therapy (LLLT) as compared to occlusive splint therapy (OST) on the TMJ opening index (TOI) and sEMG of masticatory muscles.

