**Materials and methods**

**Design**

A double-blinded parallel group randomized controlled trial. An external assessor with more than 10 years clinical experience, blinded to both treatment and results was recruited to deliver the LLLT.

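### TOI is the only primary outcome, but the one analysis the protocol fixes, a 3 x 2 mixed-design MANOVA, does not isolate a between-arm comparison of TOI

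*Protocol*

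**What the plan says.** Under Primary outcome the protocol lists one measure: "The temporomandibular opening index (TOI) is calculated by the formula", followed by the ratio of passive and maximum voluntary opening. Under Secondary outcomes it lists sEMG from six channels (left and right masseter, anterior temporal and sternocleidomastoid; the list ends "right sternocleidomastoid (RSM), and left sternocleidomastoid (LSM) muscles will be recorded") and pain: "Pain intensity will be assessed by the Visual Analogue Scale (VAS").

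The Purpose section asks for the efficacy of laser compared with splint "on the TMJ opening index (TOI) and sEMG of masticatory muscles". That is a between-arm question.

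The Statistical analysis section has three elements: the software, a homogeneity check, and one model, a 3 x 2 mixed-design MANOVA for "comparing variables in different groups and measurement times". It does not list the dependent variables or the measurement times, single out TOI, or say which effect (group, time or their interaction) carries the primary conclusion. No covariate is named.

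On size, the Subjects section says only: "Sample size was calculated through estimates for the means and standard deviations that will be obtained from a pilot study on 15 patients".

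**The concern.** The outcome section ranks TOI above everything else, and the analysis section drops that ranking. A multivariate test of several outcomes addresses one global null, that no combination of the outcomes differs. If TOI, VAS and sEMG enter together, the test can reject because of VAS or one muscle channel alone, and it can fail to reject although TOI differs.

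The wording also leaves open which effect counts. A time main effect pools both arms and cannot show that one treatment beats the other. A group main effect averages over all measurement times, including the pre-treatment value if baseline is one of them. Only a between-arm contrast after treatment, or the group-by-time interaction, addresses the stated purpose.

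At stake is the link between the primary outcome and the efficacy conclusion. As written, the analyst could choose which variable and which effect to report after seeing the results.

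A protocol may leave detail to a statistical analysis plan. Here, though, it has chosen a method, and a later plan that followed it would inherit the mismatch.

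**Working it through.** The protocol states no sample size, power, alpha or effect, so there is no figure of its own to reproduce. What follows is an illustration under stated assumptions.

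**Inputs from the protocol.** One primary outcome (TOI). Secondary: six sEMG channels and VAS. Number of dependent variables if all enter jointly: 1 + 6 + 1 = 8. Two arms are described (laser, splint), so 3 x 2 is taken as three measurement times by two arms.

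**Assumed.** Two-sided alpha 5%; 1:1 allocation; standardised TOI difference d = 0.5 or 0.8; equal correlation c between outcomes; equal correlation r between measurement times.

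**Step 1: TOI alone.** Noncentrality is (n/2)d², with n per arm.
- d = 0.5, n = 64: 32 x 0.25 = 8.00; power 80.1%.
- d = 0.8, n = 26: 13 x 0.64 = 8.32; power 80.7%.

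**Step 2: eight-variable joint test (Hotelling's T²) at the same n.** The test is F with 8 and 2n - 9 degrees of freedom: 119 for n = 64, 43 for n = 26. If only TOI differs, the noncentrality from step 1 is multiplied by (1 + 6c)/((1 - c)(1 + 7c)). If all eight outcomes shift by the same d, the multiplier is 8/(1 + 7c).

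| Scenario | Multiplier | Power, n = 64, d = 0.5 | Power, n = 26, d = 0.8 |
|---|---|---|---|
| Only TOI differs, c = 0 | 1.00 | 44.7% | 41.8% |
| Only TOI differs, c = 0.3 | 2.8/2.17 = 1.29 | 57.1% | 53.6% |
| Only TOI differs, c = 0.5 | 4/2.25 = 1.78 | 74.1% | 70.4% |
| All shift by d, c = 0.3 | 8/3.1 = 2.58 | 90.5% | 88.0% |
| All shift by d, c = 0.5 | 8/4.5 = 1.78 | 74.1% | 70.4% |

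If only TOI differs and c = 0, the joint test needs 125 per arm (d = 0.5) or 51 per arm (d = 0.8) for 80% power. The two all-shift rows concern the global null; a rejection there says nothing specific about TOI.

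**Step 3: use of baseline, TOI only.** In units of the outcome variance, the variance factor is 2(1 - r) for change from baseline and 1 - r² for ANCOVA. Their ratio is (1 - r²)/(2(1 - r)) = (1 + r)/2.

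| r | Change factor | ANCOVA factor | Ratio | Power, change | Power, ANCOVA |
|---|---|---|---|---|---|
| 0.3 | 1.40 | 0.91 | 0.65 | 66-67% | 84% |
| 0.5 | 1.00 | 0.75 | 0.75 | 80-81% | 90% |
| 0.7 | 0.60 | 0.51 | 0.85 | 95% | 98% |

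Powers cover both sizes in step 1 and are approximate: the degree of freedom spent on the covariate is ignored.

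**Step 4: which effect in a three-time TOI model.** Assume baseline is the first time and the effect is present at both later times (0, d, d). The group-by-time interaction then has about 68%, 83% and 97% power at r = 0.3, 0.5 and 0.7. For the group main effect the mean difference is 2d/3 and the variance factor (1 + 2r)/3, giving about 73%, 63% and 55-56%. Except at r = 0.3, the interaction has more power. So the choice of effect, which the protocol leaves open, matters.

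**The case against.** The strongest reply is that the joint eight-variable test is not written in the protocol. The section says only that variables are compared; it does not put them into one model or make an omnibus test the criterion for success. A mixed-design MANOVA can also mean the multivariate approach to repeated measures on one outcome at a time. The Purpose section limits the sEMG aim to masticatory muscles, so even the sternocleidomastoid channels may not belong in the model. This stands as a caution: joint analysis is the natural reading, not a stated fact. It does not rescue the section, because under either reading no TOI contrast is identified.

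Some stronger readings are tempting, and the document does not support them:
- *Baseline is ignored.* No covariate is named, but time is a within-subject factor. If baseline is one of the times, which the text does not say, the interaction compares changes from baseline. The remaining issue is efficiency against ANCOVA.
- *Power is wasted.* This cannot be shown without a sample size, effect and correlations. The loss shrinks as outcomes correlate, and joint power can exceed 80% if all respond.
- *The conclusion will rest on main effects.* Groups and times are simply the two factors, and a mixed design includes their interaction. The fault is that none of the three effects is chosen.
- *False positives on the primary outcome are inflated to about 30%.* Seven independent null follow-up tests at 5% give 1 - 0.95⁷ = 30%. That is a familywise figure; if VAS is the outcome that truly differs, six of the seven tests are secondary. A single TOI test at 5% keeps its own error at 5% or less.
- *VAS is unblinded and could drive the result.* The Design section states "A double-blinded parallel group randomized controlled trial". The present point needs no assumption about blinding.

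**Conclusion.** The point holds in a limited form. TOI is the sole primary outcome, yet the only inferential method fixed is a mixed-design MANOVA on undifferentiated variables. On its natural reading that method neither isolates TOI nor names the between-arm contrast the purpose calls for. This follows from the text and needs no power figure.

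The size is illustrative. Where TOI alone has about 80% power, the joint test ranges from 42-45% to 70-74% if only TOI differs, as the correlation between outcomes rises from 0 to 0.5. If all outcomes respond equally it is 88-91% at correlation 0.3, falling back to 70-74% at 0.5. These figures rest on assumed n, d, alpha and equal correlations, and on two arms with eight dependent variables. The gain from ANCOVA over change from baseline, a variance ratio of 0.65 to 0.85 for r from 0.3 to 0.7, presumes that baseline TOI is measured.

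This is a cheap improvement. The document does not show that the trial must fail or that its primary result would be invalid.

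**What to change.** In the Statistical analysis section:

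1. List the measurement times and name one post-treatment time as primary, for example the end of the treatment period. The protocol names none, and the analysis below depends on it.
2. Make the primary analysis an ANCOVA of TOI at that time on arm, with baseline TOI as covariate, two-sided 5%, reporting the laser minus splint difference with its 95% CI.
3. State that only this between-arm contrast supports the efficacy conclusion; within-arm changes, time effects and the group main effect do not.
4. Analyse VAS and sEMG separately with the same model, as secondary.
5. Drop the MANOVA or keep it as descriptive.

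The sample size calculation should then refer to this TOI contrast.

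Cost: statistical wording only, and SPSS, the package already named, fits the model. The one condition is that baseline TOI is among the measurements; the protocol does not list the times, so this should be confirmed.
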